### Intervention

#### Participants randomised to THUMOS (Experimental group).

Thumos is a brief, manualised cognitive-behavioural coaching programme developed specifically for medical students, involving case studies of stressful events medical students may experience on placements. It is based upon the principles of the Reboot (Recovery-boosting) coaching programme, an earlier CBT-based resilience intervention for healthcare professionals and trainees [9,22–26]. Thumos is preventative in focus, equipping students with cognitive and behavioural strategies before, rather than only in response to, the stressful events intrinsic to clinical training. It is grounded in cognitive-behavioural therapy (CBT), in which thoughts, emotions, physical sensations and behaviours are understood as interconnected, such that modifying unhelpful thinking and behaviour can improve emotional wellbeing [28,29]. It also draws on resilience theory [30]. The strategies taught are cognitive (for example, challenging negative automatic thoughts and reattributing responsibility), behavioural (for example, mood-boosting activities, problem-solving and breathing exercises) and meta-cognitive (worry postponement and gratitude). The full intervention manual is available from the authors on request.

The programme runs over four weeks and comprises two online group workshops (120 minutes each, in stable groups typically of around four to eight) and one individual coaching call (60 minutes), with an intervening practice week. All sessions are delivered remotely by qualified therapists (HCPC-registered Clinical Psychologists or BABCP-accredited CBT therapists) trained in the Thumos protocol, and participants receive a workbook in advance.

**Workshop 1** addresses the CBT model, identifying and challenging negative automatic thoughts, common unhelpful thinking habits (for example, catastrophising and mind-reading), and the role of beliefs and self-esteem. Individual exercises include mapping a personal placement stressor onto the CBT model (identifying the most distressing “hot thought”) and completing a thought record. Group-based activities include a facilitator-led formulation of a shared example and discussion of a medical-student case study to spot thinking habits.

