**Workshop 2** addresses the physiological stress response and breathing exercises, mood-boosting activities, reducing self-blame through balanced appraisals of responsibility, and a five-step problem-solving activity. Individual exercises include a guided breathing exercise, a personal mood-boosting plan, and a “responsibility pie chart”. Group-based, breakout-room activities use medical-student case studies to distinguish helpful from unhelpful behaviours and to practise responsibility appraisal and problem-solving.

**The individual coaching call** personalises the content: the facilitator reviews the strategies tried, identifies “stuck points”, and chooses from a selection of CBT-based intervention strategies (e.g., self-statements and thought challenging, gratitude, distraction, postponing worry, breathing exercises) using a decision tree, before co-producing a personal “blueprint” of takeaways and support sources.

To ensure the quality and fidelity of the Thumos intervention throughout the trial, a structured fidelity monitoring protocol is in place whereby researchers observe a minimum of 20% of workshop cycles and review recordings of 10% of individual video/phone calls, using documented fidelity assessment criteria. Therapists complete workshop diaries capturing their experiences of intervention delivery, including perceived benefits and challenges, and researcher field notes track any deviations from the protocol in real time. Participant adherence is defined as completion of both group workshops with at least 75% attendance at each session, and those who miss sessions are proactively contacted by email, text, and telephone to support engagement. The quality of qualitative process data is further strengthened through credibility strategies including respondent validation of transcripts, peer debriefing, and negative case analysis.

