### Participants Randomised to Control Group

Control condition participants will not receive an alternative intervention. However, they can continue to access mental health services that are usually available via medical schools, universities or to the public throughout the period that they are participating. A flow diagram of the participants journey through the trial can be seen in Fig 2.

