### Statistical Analysis

Analyses will use R and follow the statistical analysis plan (SAP; S2 File). Participants will be analysed as randomised, whatever intervention they receive. Those without follow-up outcomes will appear in flow and baseline summaries but not the primary outcome model. Treatment labels will remain masked until the primary dataset is locked and masked primary results are checked.

Recruitment, retention and adherence will be summarised as counts and percentages. Minimum adherence requires both workshops within six weeks of randomisation, with at least 75% attendance at each; the individual call is not required.

Baseline characteristics will be summarised by arm using means and standard deviations, medians and interquartile ranges, or counts and percentages, as appropriate. Absolute standardised differences above 0.20 will be highlighted, without significance testing or changes to prespecified adjustment covariates.

The primary outcome is BRS at four months (T3). A repeated measures linear mixed model will include BRS at T2–T4, with fixed effects for arm, categorical time, their interaction, baseline BRS, age, gender and medical school. We will use restricted maximum likelihood estimation and Kenward–Roger tests and confidence intervals. Within-participant covariance will be unstructured, or first-order autoregressive if the model fails to converge. The primary comparison is the adjusted T3 mean difference, Thumos minus services as usual, tested two-sided at α = .05. We will report adjusted arm means, mean differences and Cohen’s *d (using the pooled baseline standard deviation),* with 95% confidence intervals.

Continuous secondary outcomes will use the same approach, adjusted for each outcome’s baseline value. The two sickness absence counts will use separate Poisson mixed models with a log link and participant random intercept, or negative binomial models if overdispersed. We will report adjusted incidence rate ratios, marginal mean days lost by arm and absolute differences, with 95% confidence intervals. QALYs from baseline to T4 will be calculated as the area under the ReQoL-UI utility curve using linear interpolation. They will be compared using linear regression adjusted for baseline utility, age, gender and medical school, within multiple imputation.

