Support access will be described by arm and time, not treated as an outcome or covariate. Therapy group and therapist clustering will not be modelled. Secondary and exploratory findings will be supportive, not confirmatory. We will report unadjusted and Benjamini-Hochberg false discovery rate adjusted *p* values within separate T3 and T4 secondary outcome families [38], including BRS only at T4.

Mixed models will use available outcomes, assuming data are missing at random (MAR) given observed outcomes and covariates. We will summarise missingness patterns, response rates and stated reasons for non-response, and assess predictors using logistic regression.

Sensitivity analyses will include multiple imputation under MAR, pooled using Rubin’s rules; pattern mixture adjustments subtracting 0.10, 0.20 or 0.30 points from imputed T3/T4 BRS values in Thumos only; and carrying forward the latest observed value, using baseline if no follow-up value exists. Per protocol analyses will exclude major protocol deviations and non-adherent Thumos participants and require valid T3 BRS within 12–24 weeks of baseline.

A supplementary complier average causal effect analysis of T3 BRS will use a single instrumental variables model fitted by two-stage least squares, with allocation as the instrument for minimum adherence. Both stages will adjust for baseline BRS, age, gender and medical school. All randomised participants will be included, using multiple imputation for missing outcomes. We will report the effect and 95% confidence interval, Thumos adherence proportion and first-stage partial *F* statistic.

Residual and influence diagnostics will check model assumptions. Severe non-normality or unequal residual variances will prompt sensitivity analysis using robust standard errors clustered by participant. Robustness will be judged by consistency in the T3 effect’s direction and magnitude. Scale reliability will be reported as Cronbach’s alpha and McDonald’s omega with 95% bootstrap confidence intervals. Adverse and serious adverse events will be summarised by arm, with risk differences and 95% confidence intervals but no hypothesis tests.

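### The supplementary CACE codes partial and late Thumos attenders as untreated, so it would overstate the complier effect if their exposure helps

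*Protocol article*

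**What the plan says.** All places are in the protocol article.

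- **Model (Statistical Analysis).** The CACE for T3 BRS is one two-stage least squares model, "with allocation as the instrument for minimum adherence". On the population: "All randomised participants will be included, using multiple imputation for missing outcomes". The planned output is the effect with its 95% confidence interval, the Thumos adherence proportion and the first-stage partial F statistic.
- **Exposure (Statistical Analysis).** "Minimum adherence requires both workshops within six weeks of randomisation, with at least 75% attendance at each; the individual call is not required".
- **A second definition (Intervention, fidelity paragraph).** "Participant adherence is defined as completion of both group workshops with at least 75% attendance at each session". This one has no time limit.
- **Routes to partial, late or minimal exposure (Intervention).** "those who miss sessions are proactively contacted by email, text, and telephone to support engagement". Also, "participants receive a workbook in advance".
- **Control arm.** "Control condition participants will not receive an alternative intervention". No control access to Thumos is planned.
- **Timing.** T3 is four months after baseline, with a window of 12 to 24 weeks (Table 2 and the per protocol definition).

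**The concern.** Allocation is a valid instrument only if it affects T3 BRS solely through the exposure variable. In the Thumos arm, this means that being allocated to Thumos must do nothing for anyone coded as non-adherent.

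Under the stated rule, the non-adherent group includes a student who attended one full workshop and the call, a student who attended 70% of both workshops, and a student who completed both workshops in week 7. All three received active content before T3. If baseline and randomisation are close together, the week-7 completer has at least 12 − 7 = 5 weeks between finishing and the start of the T3 window. Assuming no effect in that person is hard to reconcile with the trial's own hypothesis.

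Any benefit in this group enters the intention-to-treat difference (the numerator), but the group is left out of the adherent share (the denominator). The resulting figure, presented as the effect among adherers, would be too large. The first-stage F statistic does not help, because it measures the strength of the instrument and not the exclusion restriction.

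**Working it through.** **The plan's own figure.** The article gives no expected adherence, no expected share of partial attenders and no expected CACE, so there is nothing to reproduce on this point. The design effect d = 0.50 (Sample size calculation) is used below only as a convenient scale for the true complier effect.

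**Assumed inputs**
- c: share of the Thumos arm meeting minimum adherence.
- p: share with partial attendance, or completing after six weeks but before T3.
- f: fraction of the full benefit that this second group gains.
- D: true effect in adherers.

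**Formula.** With no control access, two-stage least squares is close to the intention-to-treat effect divided by the adherent share:
- Intention-to-treat effect = c·D + p·f·D
- Planned CACE = (c·D + p·f·D) / c = D·(1 + p·f/c)

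**Illustration (c = 0.60, p = 0.20, f = 0.5, D = 0.50)**
- Intention-to-treat effect = 0.60 × 0.50 + 0.20 × 0.5 × 0.50 = 0.30 + 0.05 = 0.35
- Planned CACE = 0.35 / 0.60 = 0.583, against a true 0.50
- Ratio = 1 + 0.20 × 0.5 / 0.60 = 1.167, about 17% too large

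**Planned CACE when D = 0.50, for other assumed values**

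| c | p | f = 0 | f = 0.25 | f = 0.5 | f = 1 |
|---|---|---|---|---|---|
| 0.80 | 0.10 | 0.500 | 0.516 (+3.1%) | 0.531 (+6.3%) | 0.563 (+12.5%) |
| 0.70 | 0.20 | 0.500 | 0.536 (+7.1%) | 0.571 (+14.3%) | 0.643 (+28.6%) |
| 0.60 | 0.20 | 0.500 | 0.542 (+8.3%) | 0.583 (+16.7%) | 0.667 (+33.3%) |
| 0.50 | 0.30 | 0.500 | 0.575 (+15.0%) | 0.650 (+30.0%) | 0.800 (+60.0%) |

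Over c from 0.5 to 0.8, p from 0.1 to 0.3 and f from 0.25 to 1, the overstatement runs from 0.1 × 0.25 / 0.8 = 3% to 0.3 × 1 / 0.5 = 60%. The sign reverses if partial exposure harms: f = −0.25 with c = 0.70 and p = 0.20 gives −7%.

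**Simulation check.** Two-stage least squares with 220 participants, one baseline covariate, 3,000 runs, c = 0.70, p = 0.20 and D = 0.50 gave mean estimates of 0.503, 0.571 and 0.641 for f = 0, 0.5 and 1. The formula gives 0.500, 0.571 and 0.643.

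**Does recoding the exposure help?** With exposure defined as any Thumos attendance, the estimate becomes (c·D + p·f·D) / (c + p). At c = 0.70, p = 0.20 and f = 0.5 this is (0.35 + 0.05) / 0.90 = 0.444, the true mean effect among all who attended. The simulation gave 0.444. For D above zero and f between 0 and 1, (c + p·f)/(c + p) ≤ 1 ≤ 1 + p·f/c. Sampling error and workbook effects aside, the two estimates therefore bracket D.

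**The case against.** **It is conditional.** A reader might infer that the exclusion restriction certainly fails and that the CACE is certainly too large. The article does not support that. The bias needs some partial or late attenders, and it needs their exposure to help. The programme runs over four weeks, so a six-week limit leaves some slack, and the wait from randomisation to the first workshop is not stated. The late share is unknown either way. This stands, and it is why the point is worded conditionally.

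**The sizes are assumed.** This stands too. The upper figures need a large partial group with full benefit, and none of the percentages should be read as a forecast for this trial.

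**It is supplementary.** A reader might infer that the trial's main conclusion is at risk. It is not: the primary T3 comparison analyses participants as randomised and does not use adherence, and no sample size rests on the CACE.

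**The reporting is partly protective.** The adherence proportion and the primary estimate will both be shown, so a reader can see how far the CACE has been scaled up. That does not show how much of the scaling is unwarranted, because the partial and late share is not among the planned CACE outputs. Discussion of instrumental variable assumptions may sit in the unseen analysis plan, and its absence here is not the complaint. The complaint is the exposure definition, which the article fixes.

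**The two definitions.** A reader might infer that the CACE exposure is ambiguous. It is not: the model names minimum adherence, and that term is defined in the same section. The discrepancy does not cause the bias. It does leave late completers classified differently in two places, which matters for adherence reporting and for the per protocol set.

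**Replacing the exposure would go too far.** Any-attendance coding answers a different question. It also leaves a small residual violation, since the workbook arrives before any session. This supports adding an analysis rather than substituting one.

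**Conclusion.** The point holds in conditional form. As specified, the CACE treats partial and late Thumos attenders as if allocation did nothing for them, which is implausible if Thumos works. The estimate would then exceed the true complier effect by the factor 1 + p·f/c: about 17% at the assumed c = 0.60, p = 0.20 and f = 0.5, and nothing if p or f is zero. The algebra needs only that controls have no access to Thumos. The size rests wholly on assumed values, and the upward direction rests on partial exposure being beneficial. The consequence is confined to a supplementary analysis. It is still worth correcting, because the remedy is cheap and can be fixed before the primary dataset is locked and allocation is revealed.

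**What to change.** 1. Keep the minimum-adherence CACE and add a second two-stage least squares model with the same covariates and imputation. Define its exposure as any Thumos session (workshop or call) attended before T3, with no six-week limit.
2. Report the two estimates side by side, with the share of the Thumos arm that attended partially and the share that completed late.
3. Describe the minimum-adherence estimate as an upper-end value if partial exposure is beneficial, and note that the advance workbook leaves a small residual violation in both models.
4. Optionally, add a version using contact time (2 × 120 + 60 = 300 minutes at most). State that it assumes a linear dose effect and treats workshop and call minutes as interchangeable.
5. Reconcile the adherence definition in the Intervention section (no time limit) with the one in Statistical Analysis (six-week limit), and say which one defines the per protocol set.

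The cost is analysis-plan wording and one extra supplementary estimate. The 75% rule already implies that workshop attendance is recorded; recording of call attendance, and of call minutes for step 4, should be confirmed. The downside is that the added estimate describes any attendance rather than the minimum course, and it will usually be smaller.

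### The robustness criterion, direction and size of the T3 effect, cannot inform the robust-standard-error check, because that check leaves the T3 estimate unchanged

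*Protocol article*

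**What the plan says.** All the relevant text is in the Statistical Analysis section of the Protocol article.

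- **Primary inference.** "The primary comparison is the adjusted T3 mean difference, Thumos minus services as usual, tested two-sided at α = .05". On estimation: "We will use restricted maximum likelihood estimation and Kenward–Roger tests and confidence intervals".
- **Covariance.** "Within-participant covariance will be unstructured, or first-order autoregressive if the model fails to converge". The article names no covariance that differs by arm.
- **Diagnostics and response.** "Residual and influence diagnostics will check model assumptions". Then: "Severe non-normality or unequal residual variances will prompt sensitivity analysis using robust standard errors clustered by participant". This is the one analysis the article names for that trigger.
- **Criterion.** "Robustness will be judged by consistency in the T3 effect’s direction and magnitude". It mentions no standard error, interval or p value.
- **Other checks on missing data.** "Sensitivity analyses will include multiple imputation under MAR, pooled using Rubin’s rules; pattern mixture adjustments subtracting 0.10, 0.20 or 0.30 points" (applied to imputed Thumos values), followed by an analysis that carries the latest observed value forward.

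**The concern.** The robust-standard-error analysis is triggered when the diagnostics suggest that the model-based standard error may be wrong. Its purpose is to show whether the uncertainty around the T3 difference was misstated. The stated criterion looks only at the sign and size of that difference, which this analysis holds fixed. The check therefore counts as passed whatever happens to the interval.

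What is at stake is a label on the primary result. The primary claim is a two-sided test at 0.05, so the standard error helps to decide it. If the robust interval came to include zero where the Kenward–Roger interval did not, the stated rule would still describe the finding as robust.

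**Working it through.** **1. The plan's own figure.** The plan gives no number for this check. Its sample-size figure supplies the group sizes used in step 4. Take 200 participants, 100 per arm, with dropout of 30% (Thumos) and 40% (services as usual). That leaves 70 and 60 completers. For d = 0.50 and SD 1:

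- d / √(1/70 + 1/60) = 0.50 / 0.1759 = 2.842
- power = Φ(2.842 − 1.960) = 81.1%, against the stated approximately 80%
- 200 × 1.10 = 220, as stated.

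The point below does not depend on this figure.

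**2. What the robust step changes.** For participant i, let X_i be the design matrix, V_i the fitted covariance and y_i the outcomes.

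- Estimate: β = A⁻¹ Σ X_i′V_i⁻¹y_i, with A = Σ X_i′V_i⁻¹X_i
- Clustered robust variance: A⁻¹ (Σ u_i u_i′) A⁻¹, with u_i = X_i′V_i⁻¹(y_i − X_iβ)

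The robust step uses the same β and replaces only its variance. The T3 difference is one element of β, so its change is exactly 0. Direction and magnitude agree in every dataset.

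In 20 simulated trials the ratio of robust to model-based standard error ran from 0.93 to 1.00 (mean 0.97). N = 220 and the 30%/40% dropout come from the plan. The skewed errors and 2:1 SD ratio, with Thumos the more variable arm, are assumptions. Significance changed in none of the 20.

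**3. Where the criterion does work.** A pattern-mixture shift moves the T3 difference by about the shift times the fraction of Thumos T3 values imputed. With 20% to 30% imputed (assumed):

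- smallest: 0.20 × (−0.10) = −0.02 points
- largest: 0.30 × (−0.30) = −0.09 points.

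The estimate moves, so direction and magnitude say something there. Multiple imputation and carried-forward values can move it too.

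**4. How far the standard error could be off.** This is a two-group approximation at T3 with 70 Thumos and 60 services-as-usual completers. It is conservative, because the dropout is stated by T4. Thumos SD is 1; the services-as-usual SD is assumed to be 1.5.

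- Correct variance: 1/70 + 2.25/60 = 0.05179, SE 0.2276
- Common-variance version: [(69 × 1 + 59 × 2.25)/128] × (1/70 + 1/60) = 1.576 × 0.03095 = 0.04879, SE 0.2209
- Ratio: 0.2276 / 0.2209 = 1.030
- Two-sided error: 2 × [1 − Φ(1.960/1.030)] = 5.7%

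With an SD ratio of 2 the same steps give 0.08095 and 0.07375, a ratio of 1.048. If Thumos is the more variable arm at 1.5, they give 0.04881 and 0.05181, a ratio of 0.971, and the common-variance standard error is too large. The sign of the error depends on which arm varies more.

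**5. What that could do to the conclusion.** With a ratio of 1.03, significance is lost only if the primary z lies between 1.96 and 1.96 × 1.03 = 2.02, that is, p between about 0.044 and 0.05.

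A worked case with assumed values: a T3 effect of 0.32 SD with SE 0.160 gives z = 2.00, p = 0.046, 95% CI 0.01 to 0.63. With an SE 5% larger (0.168), z = 1.90, p = 0.057, 95% CI −0.01 to 0.65. The estimate is 0.32 both times, so the stated rule treats the two as consistent. The 5% is chosen to show the mechanism. The simulation in step 2 does not predict it; there the robust standard error was on average smaller.

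**The case against.** The strongest reply concerns scope. The criterion does not name the robust-standard-error check. It follows a run of sensitivity analyses on the primary outcome and can be read as covering them all, where it is an ordinary and useful rule. That stands, and step 3 supports it. But whether the sentence covers all the analyses or only the one just before it, it is uninformative for the robust-standard-error check.

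A reader might infer three stronger points that the documents do not support.

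- *That robust standard errors are the only remedy planned.* They are the only one the article names for this trigger. The article defers to a statistical analysis plan that is not shown and may name others.
- *That the check discards the small-sample correction of the primary analysis.* The article does not say which clustered variance or degrees of freedom will be used. That detail is commonly left to the analysis plan, so its absence is no defect here.
- *That the primary result is likely to be overturned.* The simulated robust standard errors were no larger than the model-based ones, and near-balanced arms keep the error rate close to nominal. A change of conclusion needs a result already near 0.05.

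It is also fair that judging sensitivity analyses by effect size rather than significance is a defensible preference, and that nothing prevents the robust interval from being reported. Both limit the harm. Neither gives the stated criterion any content for this check. Robust standard errors could in principle mean refitting under another working covariance, which would move the estimate (by at most 0.034 BRS points in the simulations, using independence), but the article does not say so.

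**Conclusion.** The point holds for one analysis. Applied to participant-clustered robust standard errors on the fitted mixed model, the direction-and-magnitude criterion is met by construction, so it cannot detect the problem that triggers the check. This follows from algebra and rests on one assumption: that the robust variance is computed on the planned model without refitting its covariance, as the wording implies.

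The consequence is modest. The analysis runs only if violations are severe, and the primary conclusion rests on the Kenward–Roger test. Under the assumed SD ratio of 1.5 with services as usual the more variable arm, the standard error would be about 3% too small and two-sided error about 5.7%. The plan should be corrected because the fix is nearly free, not because the primary analysis is unsound.

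**What to change.** In the analysis plan, and in the article if it is revised:

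1. State which sensitivity analyses the direction-and-magnitude criterion covers. Keep it for those that can move the T3 estimate: multiple imputation, pattern mixture and carried-forward values.
2. For the robust-standard-error check, report the robust 95% interval and p value beside the Kenward–Roger results. Judge robustness on whether the interval, and the conclusion drawn from it, materially changes. A material change is better than a bare switch across 0.05, which a trivial difference could decide.
3. If residual variances differ by arm, also refit with an arm-specific covariance. This reweights the data and can move the estimate, so both criteria then apply.
4. Preferably name a small-sample-corrected clustered variance (for example CR2 with Satterthwaite degrees of freedom). This is advice, not correction of a stated error.

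The cost is a few sentences, at most one extra model fit and a little more reporting, with no new data. The last follow-up assessments are expected by February 2027, so the wording can be settled before the primary dataset is locked and allocation revealed.
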